The primary objective of this study is to determine if feedback about characteristics of daily walking activity, provided to patients and their treating therapists, will increase walking activity in a group of individuals receiving rehabilitation post-stroke. We hypothesize that, compared to a control group who do not receive feedback via the treating physiotherapists, those who receive accelerometer-based feedback of daily walking activity as part of a goal-setting process will show: increased total daily walking activity, as measured by number of steps per day, total duration of walking activity, and total distance walked; increased frequency of ‘long’ walking bouts (i.e. > 5 minutes in duration); and improved control of walking, as defined by increased self-selected walking speed, and improved symmetry in spatio-temporal characteristics of walking. While walking practice should be initiated during in-patient rehabilitation, problems with walking function may not be fully apparent until the patient is discharged home. Therefore, we will examine the effects of accelerometer-based feedback administered during both in- and out-patient rehabilitation. Under the assumption that accelerometer-based feedback will increase walking activity, the secondary objective of this study is to determine if increased walking activity during rehabilitation results in increased rates of goal attainment, increased satisfaction with rehabilitation, improved self-efficacy, and improved community re-integration post-discharge from rehabilitation.

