## Methods

### Design overview

This is a single-blind randomized controlled trial with the assessor being blinded to the group allocation (participants cannot be blinded to group allocation). Participants will be randomly assigned, using allocation concealment, to one of two groups: feedback or no feedback. The study will span three phases of rehabilitation and recovery post-stroke: in-patient rehabilitation, out-patient rehabilitation, and post-rehabilitation community reintegration. Outcome measures will be obtained at up to four time points (Figure 2): 1) upon entry into the study; 2) immediately prior to discharge from in-patient rehabilitation; 3) immediately prior to discharge from out-patient rehabilitation (for those admitted to out-patient rehabilitation at the institution); and 4) three months following discharge from rehabilitation. This study was approved by the University Health Network research ethics board (protocol number 11-027-DE).

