**Figure 2 F2:**
[figure not shown]
**Participant flowchart.** The study will span three phases of rehabilitation and recovery post-stroke: in-patient rehabilitation, out-patient rehabilitation, and post-rehabilitation community re-integration. Patients will be assessed for eligibility upon admission to in-patient rehabilitation and throughout their stay. Upon providing consent, participants will be assigned to either the feedback or no feedback group. Participants who are discharged to out-patient rehabilitation at one of Toronto Rehab sites will continue to complete the schedule of goal-planning for walking activity either with or without feedback (depending upon group allocation).

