#### In-patient rehabilitation phase

Participants in both intervention groups will meet with their primary treating physiotherapist once per week to discuss progress towards their goals for rehabilitation that are relevant to physiotherapy, including goals for walking. All participants will wear the accelerometers every weekday during in-patient rehabilitation to monitor daily walking activity. Research personnel will meet with the patients each morning to ensure that the accelerometers are worn correctly.

For those participants assigned to the feedback group, physiotherapists will receive a daily summary of patients’ walking activity as a tool to guide goal planning. Physiotherapists will use the information as a ‘homework checker’ to determine if patients are complying with an assigned walking program. In the case of non-compliance, the physiotherapist will discuss a coping strategy for better integrating walking activity into the patients’ day. In the event that the patient is meeting their specific sub-goals for walking activity, the physiotherapist will re-evaluate these sub-goals and suggest more challenging goals.

For participants assigned to the control group, physiotherapists will not receive accelerometer-based feedback of daily walking activity. However, physiotherapists will still discuss the achievement of walking goals with their patient. The same strategies implemented in the feedback group will be implemented in the control group (i.e. action plans, coping strategies, re-evaluation of goals). This process is no different to usual care around goal planning at Toronto Rehab.

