### Statistical analyses and sample size

The following potentially confounding measures will be compared between the two intervention groups: CMSA, BBS, NIH-SS, ABC, and length of stay (in-patient rehabilitation). Measures that differ significantly between the two groups will be included as covariates in statistical models comparing interventions. Repeated-measures analysis of variance (ANOVA) or analysis of covariance (ANCOVA; as appropriate), with group-by-time interaction, will be used to evaluate the effect of the interventions on walking activity, spatio-temporal characteristics of walking, and SEQ. Separate ANOVAs will be used for each outcome measure. The ‘group’ term is the intervention group; the ‘time’ term is the assessment time point. The group-by-time interaction effect will reveal if there is a greater change over time in one group compared with the other. Separate analyses will be conducted to compare measures at the first three time points; i.e. discharge from in-patient will be compared to study enrolment, and discharge from out-patient will be compared to discharge from in-patient. One-way ANOVA or ANCOVA will be used to compare the CIQ and satisfaction between the two groups at discharge from rehabilitation and three months post-discharge from in-patient. The frequency of goal attainment between the two groups will be compared at discharge from both in-patient and out-patient rehabilitation; intent-to-treat analysis will be employed for this outcome for all participants initially randomized, including those who withdraw from the study [24,57]. Barriers to walking will be documented.

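### The only stated test at out-patient discharge starts from in-patient discharge, so it measures added change in that phase and not the cumulative effect of feedback; a contrast with enrolment is needed

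*Protocol article*

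**What the plan says.** The objectives at the end of the Background cover the whole course of rehabilitation: "we will examine the effects of accelerometer-based feedback administered during both in- and out-patient rehabilitation". Randomisation takes place once, during the in-patient stay (Figure 2 legend): "Upon providing consent, participants will be assigned to either the feedback or no feedback group". The intervention starts in that stay. For the feedback arm, "physiotherapists will receive a daily summary of patients’ walking activity as a tool to guide goal planning" (In-patient rehabilitation phase).

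The section on primary outcomes measures walking activity at three points: enrolment (Time 1), in-patient discharge (Time 2) and out-patient discharge (Time 3). The Design overview limits the third: "immediately prior to discharge from out-patient rehabilitation (for those admitted to out-patient rehabilitation at the institution").

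Under Statistical analyses and sample size, repeated-measures ANOVA or ANCOVA with a group-by-time interaction "will be used to evaluate the effect of the interventions on walking activity, spatio-temporal characteristics of walking, and SEQ". The interaction is interpreted as follows: "The group-by-time interaction effect will reveal if there is a greater change over time in one group compared with the other". Two pairwise analyses are then listed: "discharge from in-patient will be compared to study enrolment", and "discharge from out-patient will be compared to discharge from in-patient". Time 3 is not compared with Time 1. The candidate covariates are CMSA, BBS, NIH-SS, ABC and in-patient length of stay, each used only if the arms differ on it. Enrolment walking is not among them.

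**The concern.** Time 2 is an outcome of the randomised intervention. By then the feedback arm has had an in-patient phase of roughly 2 to 4 weeks, and the sample size assumes that its walking time has risen by 40 minutes against 20 in control. When Time 2 is the reference for Time 3, the difference the trial hopes to produce is subtracted from the out-patient result.

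The remaining quantity is the difference between arms in what happened after Time 2. That is not the effect of feedback given over both phases, which the objectives ask about and which Time 3, as a primary-outcome time point, is there to show. If feedback produces a gain that lasts to out-patient discharge, no stated test is directed at finding it there.

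**Working it through.** **1. The protocol's sample size.** Inputs from Statistical analyses and sample size: difference 20 minutes, SD of change 23 minutes, Type I error 0.05 (taken as two-sided), Type II error 0.1.

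n per arm = 2 × [23 × (1.960 + 1.282) / 20]² = 27.8, rounded up to 28. This reproduces the stated figure. The sizing uses the Time 1 to Time 2 change, so the point below does not touch it.

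**2. What each contrast estimates.** The arms have equal expected values at Time 1 by randomisation. Let the true difference between arms (feedback minus control) be 20 minutes at Time 2, the design effect, and D at Time 3.

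- Planned interaction, Time 3 vs Time 2: D − 20
- Enrolment contrast, Time 3 vs Time 1: D − 0 = D

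The planned contrast is 0 when D = 20 and negative for every D below 20, even while feedback patients still walk more. This part needs no assumption about variance.

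**3. How often each is significant.** Two assumptions are needed that the protocol does not supply: the SD of 23 minutes, a pilot value for Time 1 to Time 2, also holds for both Time 3 contrasts; and all 28 per arm reach Time 3.

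SE = 23 × √(2/28) = 6.15 minutes. The chance of a significant result in favour of feedback is Φ(contrast/SE − 1.96); against feedback it is Φ(−contrast/SE − 1.96).

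| D at Time 3 | Time 3 vs Time 2 | Favours feedback | Greater gain in controls | Time 3 vs enrolment | Favours feedback |
|---|---|---|---|---|---|
| 20 | 0 | 2.5% | 2.5% | +20 | 90% |
| 15 | −5 | 0.3% | 13% | +15 | 68% |
| 10 | −10 | <0.1% | 37% | +10 | 37% |
| 5 | −15 | <0.1% | 68% | +5 | 13% |

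A t-test simulation of 20,000 trials per row (correlation 0.5 between visits) agreed to within about 2 percentage points. For example, it gave 89% for the enrolment contrast at D = 20, and 36% in each direction at D = 10.

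**4. Sensitivity to the two assumptions.** Only participants admitted to out-patient care at the institution have Time 3 data, and the protocol gives no admission rate.

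- SD 23, 21 per arm (three quarters): SE = 23 × √(2/21) = 7.10. Enrolment contrast at D = 20: 80%. Significantly greater gain in controls under the planned test at D = 10: 29%.
- SD 23, 14 per arm (half): SE = 23 × √(2/14) = 8.69. The same two figures: 63% and 21%.
- SD 30, 28 per arm: SE = 30 × √(2/28) = 8.02. The same two figures: 70% and 24%.

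At D = 20 the planned test stays at 2.5% in each direction throughout, because its expected value is 0.

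**The case against.** **The sized comparison is untouched.** Total walking duration from enrolment to in-patient discharge is the outcome used for the sample size. It is referenced to the randomised baseline and has about 90% power. A reader might infer that the trial cannot answer its question; the documents do not support that. What is missing is a cumulative test at Time 3. This objection stands.

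**Time 3 vs Time 2 is a fair question.** The study is built in phases, with daily summaries to physiotherapists in the first and weekly ones in the second. Whether feedback adds gain in the out-patient phase is worth asking, and 0 is the right answer when an advantage is held without growing. This stands too, but it does not make that contrast an answer about feedback over both phases.

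**A negative interaction is not harm.** A reader might infer that a partly kept benefit would be reported as harm. By the protocol's own definition, the result would mean that controls changed more in that phase, and it would appear beside the in-patient result. Even with half the advantage kept, about 63% of trials show no significant interaction.

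**The same ANOVA has a group term.** Suppose a between-person SD of 20 minutes (an assumption) and a per-visit residual variance of 23²/2 = 264.5. The mean of Times 2 and 3 then has SD √(400 + 264.5/2) = 23.1 and SE 6.17. The expected group effect is 20 minutes if all is kept and (20 + 10)/2 = 15 if half is kept, detected in about 90% and 68% of trials. A lasting difference would thus be visible. However, the protocol reads the effect from the interaction, and this term mixes Time 2 with Time 3.

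**The advantage might grow.** If it rose from 20 to 30 minutes, the planned contrast would be +10 and favour feedback in about 37% of trials. The table covers only sustained or fading advantages, and the protocol predicts neither.

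**Selection into out-patient care is a separate matter.** It affects the enrolment contrast as well, and changing the reference point does not cure it.

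**Conclusion.** The point holds in a limited form. For walking activity, gait and stroke self-efficacy, the only stated test at out-patient discharge measures incremental change from a post-randomisation value. It does not estimate the cumulative effect of feedback. That its expected value is 0 or below when the design advantage is fully or partly kept is arithmetic and does not depend on the SD.

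The frequencies (2.5% against 90% when fully kept; 37% for controls against 37% for feedback when half is kept) rest on an SD of 23 minutes for the Time 3 contrasts and on all 28 per arm reaching Time 3. Because not everyone will reach Time 3, the power figures are upper values for that SD. The in-patient comparison and the sample size stand as written.

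**What to change.** Make the test of the overall effect at out-patient discharge a contrast with enrolment. Either compare Time 3 with enrolment, or fit one longitudinal model to Times 1 to 3, adjusted for enrolment value and walking-speed stratum, with group contrasts at Time 2 and Time 3. Keep Time 3 vs Time 2 as a phase-specific, descriptive contrast, worded as added change during out-patient care.

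Report out-patient admission by arm, and state that any Time 3 contrast is made in a subset formed after randomisation.

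The cost is a change of analysis wording and one more contrast to report. No extra data, visits or participants are needed, and the sample size does not change.

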## Discussion

While there has been interest in using accelerometers for walking-related goal-setting and goal-planning in rehabilitation, the effectiveness of this technology in clinical practice to improve walking activity has not been shown. This study may demonstrate that accelerometer-based feedback of walking activity can increase walking activity, improve walking outcomes, and potentially improve community re-integration following discharge from stroke-rehabilitation. The study design deliberately integrates the novel intervention into current practice; therefore, the results will be immediately generalizable to other stroke rehabilitation settings.

## Abbreviations

ABC: Activity-specific balance confidence questionnaire; ABLE: Accelerometry for Bilateral Lowe Extremities; ANCOVA: Analysis of co-variance; ANOVA: Analysis of variance; BBS: Berg balance scale; CIQ: Community integration questionnaire; CMSA: Chedoke-McMaster Stroke Assessment; ICC: Intraclass correlation coefficient; SEQ: Stroke self-efficacy questionnaire.
